### Plans to Promote Participant Retention and Complete Follow-Up

#### Survivors of Burn Injuries

To promote completion of the follow-up questionnaires, a researcher will remind participants a maximum of 2 times if they have not completed the questionnaires. These reminders can be an email or a phone call. We will adhere to an intention-to-treat approach. If treatment at the burn center is concluded before the survivor of burn injuries has been through all the BreeZe phases, the questionnaires will continue to be sent, except when a survivor of burn injuries withdraws their consent to participate.

#### Health Care Professionals

Health care professionals will be reminded by the responsible researchers to complete questionnaires, to select consultations for the video observations, and to set a date for the interviews.

### Data Management

The responsible researcher of each center will save data in password-protected Microsoft Excel files, which are stored on a protected working drive. Passwords of the files are only known by the involved researchers. Data will be stored for 15 years according to the Dutch Personal Data Protection Law.

#### Survivors of Burn Injuries

Eligible survivors of burn injuries will be identified by the nurse practitioners or aftercare nurses, which will be communicated with the research team. For entry in the password-protected eligibility file, the characteristics documented are name, patient number, date of admission, date of surgery, date of discharge, and participation (yes or no, with reason if no).

Informed consent will be taken on paper and stored in a locked cupboard at the research office of each burn center. After the informed consent has been taken, each survivor of burn injuries will be assigned a unique study code which will be entered in a password-protected key data file in Excel containing key, name, and patient number.

Questionnaires will be sent out via Lighthouse QuestManager. Data will be extracted in an Excel file and then transported into IBM SPSS (version 25 or higher versions).

#### Health Care Professionals

Information on eligible health care professionals will be included in a password-protected eligibility file in Excel, which will be stored on a protected working drive. The password of the eligibility file is only known by the involved researchers. For entry in the eligibility file, the characteristics of eligible health care professionals that are documented are name, years of experience within the profession (divided into categories), and participation (yes or no).

Informed consent will be taken on paper and stored in a locked cupboard at the research office of each burn center. After taking informed consent, each health care professional will be assigned a unique study code in a password-protected key data file in Excel.

Questionnaires will be sent out on paper or via Castor [60]. Data from paper questionnaires will be imported into an Excel file and then transported into SPSS or MLwiN (Center for Multilevel Modelling, University of Bristol) [57]. Video recording files will be directly transferred from the video camera to the research working drive. Interview recordings will be directly transferred from the tape recorder to the research working drive, and then transported into Atlas.TI.

### Statistical Methods

#### Statistical Methods for Primary and Secondary Outcomes

##### Overview

All quantitative analyses will be conducted using MLwiN 3.10 for nested data or IBM SPSS Statistics [57]. A *P* value <.05 will be considered statistically significant. For all outcomes, descriptive statistics will be used to present demographics and outcomes, using frequencies (%) for categorical variables, and median and IQR (if nonnormally distributed) or mean and SD (if normally distributed) for continuous variables.

##### RE-AIM: Reach

To examine if participating survivors of burn injuries are representative of the general survivor of burn injuries population, baseline demographics of participating survivors of burn injuries and nonparticipating survivors of burn injuries will be compared using chi-square tests for categorical data, and Mann-Whitney or independent *t* tests for numerical data.

##### RE-AIM: Effectiveness

###### Effectiveness on Health Outcomes of Survivors of Burn Injuries – Coprimary Outcome Measure

To examine if participants in the control and intervention groups are comparable on baseline demographics and clinical outcomes, chi-square tests will be used for categorical data, and Mann-Whitney or independent *t* tests will be used for numerical data. To test the effectiveness of BreeZe on health outcomes of survivors of burn injuries, we will conduct (multilevel) regression analyses for repeated measurements, with measurement occasions nested in patients. Variables that might explain differences between measurement occasions (eg, time since injury, time since discharge, season, and time since intervention started) or patient (eg, age and sex) will be tested. We expect that the variance between measurement occasions will be largely explained at the level of patients. To account for the difference between centers, we will add 2 dummy variables (with center 1 being the reference center) to these analyses [55].

In addition, as control and intervention participants are enrolled in different calendar periods in different centers due to the stepped-wedge design, we will test in the (multilevel) regression analyses whether time can best be modeled continuously (since discharge) or as a categorical variable. The latter is interpreted more easily and is more often used in clinical settings, but does increase the degrees of freedom in the model. We will also document major changes in burn care organization, staffing, or parallel initiatives during the study and consider these in sensitivity analyses and in the interpretation of our findings.

The primary data analyses will be conducted on the data of the PiH questionnaire. In the multilevel analyses, the patient’s PiH score at a certain moment is the dependent variable. In addition, we will use three different approaches to provide a comprehensive evaluation of the intervention’s impact. First, for each group, the number and percentage of participants who have improved by at least 8 points on their self-management skills will be calculated, and the difference between groups will be tested with a chi-square test. We consider an improvement of 8 points a clinically relevant score, based on a face validity assessment by burn care nurse practitioners.

Second, to examine whether greater improvement is achieved by individuals with low compared with high baseline scores, we will create 2 groups based on the median score. Besides a baseline effect and an intervention effect, an interaction effect will be tested.

Third, for each participant, we will tally the number of PiH questions where they score 6 or higher, as such a score will be considered clinically satisfactory. This sum score will range from 0 to 12 and will also be used as a dependent variable in a regression analysis with group and time as possible predictors. Our hypothesis is that there will be an increase in this sum score, which will be greater in the intervention group compared to the control group.

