### Objectives

In this paper, we provide insight into the study protocol that we aim to use to evaluate the BreeZe intervention in Dutch burn care. For more detailed information about the development of the BreeZe intervention, including preliminary feedback regarding acceptability and feasibility, we refer readers to a separate article by Geelen et al [17].

The coprimary objectives of the evaluation study are (1) the effectiveness of the BreeZe intervention in improving self-management skills in survivors of burn injuries, and (2) the effects of our implementation approach on the implementation outcomes reach, adoption, implementation, and maintenance. The secondary objectives will be to evaluate the effectiveness of the BreeZe intervention on more latent health outcomes (eg, return to work or school) and to assess the cost-effectiveness of the BreeZe intervention from a societal perspective.

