## Methods

### Trial Design

This multicenter stepped-wedge hybrid type II effectiveness-implementation study is designed to test the effectiveness of the BreeZe intervention while also testing the effect of our implementation approach [23,24]. The study is structured within a superiority framework, meaning we will systematically compare outcomes between the control and intervention groups, as well as assess changes from baseline to follow-up.

All 3 specialized Dutch burn centers will participate in this study—Martini Hospital Groningen (center 1), Red Cross Hospital Beverwijk (center 2), and Maasstad Hospital Rotterdam (center 3).

This study has 3 phases and uses in all 3 phases the implementation science frameworks “Consolidated Framework for Implementation Research” (CFIR) and the “Reach, Effectiveness, Adoption, Implementation, and Maintenance” (RE-AIM) [25-27].

In the first phase, the preimplementation phase, we will use the CFIR to provide insight into the context-specific determinants for implementing the BreeZe intervention, thereby informing the development of a context-specific implementation approach. Meetings will be held with burn physicians, nurse practitioners, aftercare nurses, and burn center managers. The findings will build on the preliminary feedback regarding acceptability and feasibility received during the development of the BreeZe intervention [17]. In addition, during the preimplementation phase, we will recruit patients to form a control group to evaluate effectiveness. This preimplementation phase starts for all 3 specialized burn centers in April 2024. Although protocol registration was finalized after the start of data collection in the preimplementation phase, we confirm that no modifications to predefined outcomes or analyses were made based on data collected before registration.

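### Time since the intervention started is listed as an ordinary candidate covariate for the PiH model, but it measures exposure to BreeZe; kept uncentred, with controls at 0, it stops the group term from being the average effect

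*Protocol article*

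**What the plan says.** The Objectives section names as a coprimary aim "the effectiveness of the BreeZe intervention in improving self-management skills in survivors of burn injuries". The analysis section for the coprimary effectiveness outcome plans a repeated-measures regression, with occasions within patients and two centre dummies, in which "the patient’s PiH score at a certain moment is the dependent variable".

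The same section says that "Variables that might explain differences between measurement occasions" will be tested, and gives as examples "eg, time since injury, time since discharge, season, and time since intervention started". It does not say whether the last clock starts at the centre's go-live or at the patient's own first BreeZe contact, what value control patients take, whether the variable is centred, or which coefficient is the BreeZe effect once it is in the model.

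Under Trial Design, "during the preimplementation phase, we will recruit patients to form a control group to evaluate effectiveness". Go-live follows in June, September and November 2024 in the three centres. The Sample Size section powers the study on a mean difference of 8 points between control and intervention groups.

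**The concern.** Time since injury, time since discharge and season exist for every patient and are sensible adjustment variables. Time since the intervention started is different: it is a dimension of the treatment. With controls at 0, entering it beside the group term adds a group-by-exposure interaction. The group coefficient is then the BreeZe effect at zero exposure, either on the centre's go-live day or at the start of the patient's own sessions, depending on the clock.

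The Sample Size section is built on an average contrast of 8 points. If the effect grows as staff gain practice or as the patient works through the sessions, the term tends to be significant and is kept. That is also when the group coefficient departs most from the average. An intervention that meets its target on average could then be reported through a coefficient near zero. If the effect fades, the coefficient is too large.

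**Working it through.** **Inputs from the protocol article.** Effect 8 points, two-sided 5% level, 80% power, control:intervention ratio 0.625:1, 20% inflation, planned 57 + 89 (Sample Size); enrolled 42 + 53, recruitment to 30 June 2025 (Results); control recruitment from April 2024 and the go-live months above (Trial Design); assessments at 2 weeks, 6 and 12 months after discharge (Data Collection Methods). The article gives no SD, within-patient correlation or recruitment pattern, so these are assumed.

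**1. The planned sample size.** Controls = (1 + 1/1.6) × (1.96 + 0.84)² × SD²/8². With SD 15 this is about 44.8, so 45 controls and 45 × 1.6 = 72 intervention patients. Dividing by 0.8 gives 57 + 90 = 147, against the stated 57 + 89 = 146. An SD near 15 therefore fits the plan, although it is not stated.

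**2. What the group term means.** Let G be group and T exposure time (0 in controls), with terms βG + γT. The effect at exposure t is β + γt, and the average effect is β + γT̄, where T̄ is the mean among intervention observations. Hence β = average − γT̄.

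| True effect (average 8) | γT̄ | β |
|---|---|---|
| Constant | 0 | 8 |
| Grows from 0 | 8 | 0 |
| Grows from 4 | 4 | 4 |
| Fades from 12 | −4 | 12 |

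Centring replaces T by T − T̄ for intervention observations and leaves controls at 0. Then β is the average in every row.

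**3. Cost if the term is always in the model.** For one occasion and exposure spread evenly from 0, T̄²/var(T) = 3, so the intervention part of the variance is multiplied by 4. At 42 + 53 the standard error rises by √[(1/42 + 4/53)/(1/42 + 1/53)] = 1.53. With SD 15 and a constant 8-point effect, power falls from about 73% to 39%.

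The planned model has three occasions and centre dummies. On the article's calendar (SD 15.3, correlation 0.6, uniform recruitment, no dropout, centre clock, controls 0) the loss for a constant effect is smaller:

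| N | SE without → with | Power without → with |
|---|---|---|
| 57 + 89 | 2.34 → 3.10 | 93% → 73% |
| 42 + 53 | 2.88 → 3.81 | 79% → 56% |

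At 57 + 89, with an effect growing from 0 at go-live to an average of 8, the group term is 7.7 without the variable, 0.0 with it uncentred and 8.0 with it centred. Across the scenarios examined, the centred version gives 7.7 to 8.5 with the SE unchanged at 2.34.

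**4. Cost if the term is kept only when p < 0.05.** This is closer to what the article says. Repeated-measures simulation on the same calendar, 42 + 53, SD 15, correlation 0.5, ranges over the clocks tried:

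| True effect | Power without the variable | Power with selection |
|---|---|---|
| Constant 8 | about 82–85% | about 80–83% |
| From 4 to average 8 | about 80–85% | 39–58% |
| From 0 to average 8 | about 80% | 6–18% |

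In the last row the mean group term is about 0 to 0.6. Centring restores about 8.

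**The case against.** The variable is only an example of something to be tested, in an article that condenses a fuller plan. The article does not say that the variable will be retained, nor that the BreeZe effect will be read from a model that holds it. That stands, and it makes the point conditional. It does not dispose of it, because the article does commit to testing a treatment-exposure variable on the same footing as season, and step 4 shows serious harm under selection when the effect grows.

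A reader might go further in four ways that the documents do not support.

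- **That only intervention patients have the variable and that time zero is go-live day.** These belong to different clocks. On the patient's own clock only intervention patients have a value, but zero is that patient's BreeZe start. On a centre clock zero is go-live, but about 93% of control occasions at 6 months and 100% at 12 months fall after it, so controls have values unless they are set to 0. If each occasion simply takes its signed centre-clock value, a constant effect of 8 is still recovered, though at 57 + 89 the SE rises from 2.34 to 3.82.
- **That power collapses whatever the true effect.** The large loss for a constant effect needs the term forced into the model. With selection in the single-occasion set-up of step 3 (SD 15, 42 + 53), the term is kept about 5% of the time and power goes from 73% to 72%.
- **That the trial would find nothing.** In the same set-up with an effect growing from 0 to 16, a joint test of group and exposure slope rejects 86% of the time. The harm arises when the uncentred group coefficient alone is read as the BreeZe effect.
- **That the variable has to be removed.** Centring keeps the average effect as the group term equally well.

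**Conclusion.** The point holds in conditional form. The article lists a measure of exposure to BreeZe as an ordinary candidate covariate in the model for its coprimary effectiveness outcome. It does not fix the clock, the control value or the centring. If the variable is retained uncentred with controls at 0, the group coefficient is the effect at time zero and no longer the average contrast behind the sample size.

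The size depends on the shape of the true effect, which is unknown. A constant effect brings no bias and almost no loss under selection, a growing effect brings understatement and a large loss of power, and a fading effect brings overstatement. The power figures rest on the assumed SD, correlation and recruitment pattern. The direction follows from the coding alone. With 42 + 53 = 95 patients enrolled of 146 planned, there is little power to spare.

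**What to change.** Before the analysis begins (planned for August 2026), do one of the following in the primary PiH model:

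- take time since the intervention started out of the candidate covariates; or
- allow it only as exposure time with a stated origin, centred at its mean among intervention observations and set to 0 for controls.

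In either case, state that the group term is the average BreeZe effect and is the primary estimate. Examine change of the effect with exposure in a secondary model, and report the effect across the observed range of exposure.

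The cost is one wording change and one extra secondary model. If the variable is removed, the primary model no longer describes learning or fading, and the secondary model does so instead.

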The second phase, the implementation phase, introduces and implements the BreeZe intervention for which we will use a stepped-wedge approach, visualized in Figure 1. We will begin by introducing the BreeZe intervention using the context-specific implementation approach developed in the preimplementation phase at center 1, in June 2024. Next, we will introduce the BreeZe intervention in center 2 in September 2024 and in center 3 in November 2024, respectively. Based on our development of the BreeZe intervention, we recognize that this implementation phase will require, at a minimum, education and training of health care professionals on how to apply the BreeZe intervention in routine clinical care. We anticipate that this implementation phase, consisting of training and intervention initiation, will take approximately 1 week; the intervention will then be delivered continuously.

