A last methodological consideration in designing this study is our aim to strike a careful balance between internal and external validity, ensuring that the study is both generalizable to different burn care settings and sufficiently rigorous and robust to provide reliable answers to our research questions. While a parallel cluster randomized design is often considered the gold standard for minimizing bias and ensuring strong internal validity, we opted for a nonrandomized stepped-wedge design [24,76,77]. A parallel cluster randomized design, in which all clusters are randomly assigned to either the intervention or control condition, is often challenging in real-world settings, as it requires immediate and simultaneous implementation across all centers. Implementation success strongly influences the outcomes of an intervention, and whether you achieve implementation success is strongly dependent on organizational readiness [59]. Also, a parallel cluster randomized design is potentially less acceptable for stakeholders, as at least 1 cluster acts as the control group, meaning they are not exposed to the potential benefits of the intervention [24,78]. In contrast, a nonrandomized stepped-wedge design allows for a staggered implementation, where all centers eventually receive the intervention but at different time points and is logistically feasible [24]. Hence, to increase stakeholder acceptability and organizational readiness, we made the choice not to randomize. However, a nonrandomized stepped-wedge design carries a greater risk of bias, particularly due to lack of randomization, time-related confounders, and potential differences between early and late adopters [79,80]. To control for these, we took fixed-time effects into account in our sample size calculation [81].

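### The primary PiH model commits to no calendar-time term, so secular drift can enter the BreeZe estimate

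*Protocol article*

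**What the plan says.** All references are to the protocol article.

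- **Roll-out.** Under Trial Design, control recruitment starts in all three centers in April 2024. BreeZe starts in center 1 in June 2024, and then: "Next, we will introduce the BreeZe intervention in center 2 in September 2024 and in center 3 in November 2024, respectively". Recruitment ends on 1 July 2025.
- **The problem, as stated.** The section on the coprimary effectiveness outcome gives as its reason for modelling time that "control and intervention participants are enrolled in different calendar periods in different centers due to the stepped-wedge design".
- **The remedy, as stated.** The same sentence continues: "we will test in the (multilevel) regression analyses whether time can best be modeled continuously (since discharge) or as a categorical variable". The section adds that the categorical form is easier to interpret and more usual in clinical settings, but does not say what the categories are.
- **Committed terms.** Measurement occasions are nested in patients, and for center "we will add 2 dummy variables (with center 1 being the reference center) to these analyses".
- **Candidate terms.** Variables that might explain differences between occasions will be tested: "eg, time since injury, time since discharge, season, and time since intervention started".
- **Known events.** Major changes in organization, staffing or parallel initiatives will be documented and considered in sensitivity analyses and in interpretation.
- **Sample Size.** One 20% adjustment covers dropout, missing data and fixed time effects together.
- **Methodological Considerations.** After conceding time-related confounding, the text says: "To control for these, we took fixed-time effects into account in our sample size calculation".
- **Secondary outcomes.** These are to be analysed with similar models.

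**The concern.** The stated problem and the stated remedy concern two different clocks. The problem is calendar time: within each center, treatment status changes once, on one date. The remedy is the form of follow-up time, which runs alike in both groups (2 weeks, 6 months, 12 months) and cannot tell an April 2024 discharge from a May 2025 discharge.

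The staggered start is the one design feature that can separate BreeZe from a general change in burn aftercare, and it does so only if the model contains a calendar term. With center dummies alone, the analysis is a pooled within-center before-after comparison. The order of the centers was chosen by perceived readiness, and there is no blinding, so the design offers no other protection. If PiH scores were drifting for other reasons, the drift would be reported as part of the BreeZe effect on a coprimary outcome. The secondary outcomes would share the problem.

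**Working it through.** **Inputs.** Month 0 is April 2024 and recruitment ends at month 15. BreeZe starts in June, September and November 2024, that is at months 2, 5 and 7 if at the start of the month, up to 3, 6 and 8 if at the end. The target difference is 8 PiH points. Assumptions that the documents do not supply: even accrual, equal centers, one measurement per patient, a linear drift common to the centers, and enrolment date standing in for discharge date.

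**Step 1: the plan's own figure.** The stated size is 57 + 89 = 146. The SD is not given, so this can only be back-solved. With 20% loss the evaluable numbers are 57 × 0.8 = 45.6 and 89 × 0.8 = 71.2, and SD = 8 / [2.80 × √(1/45.6 + 1/71.2)] ≈ 15. An SD of 15 gives 45 and 72, inflated to 57 and 90. The plan is therefore consistent with a two-group comparison plus 20%.

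**Step 2: the calendar gap with center dummies only.** For a center that starts BreeZe at month g, mean control enrolment is g/2 and mean intervention enrolment is (g + 15)/2. The difference is 15/2 = 7.5 months for every g. It needs even accrual only within each phase; the rates before and after may differ. Any weighted average over centers is also 7.5, so

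bias = 7.5 × drift per month.

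The drift rate is illustrative:

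| Drift (PiH points/month) | Bias (points) | Share of 8 points |
|---|---|---|
| 0.25 | 1.9 | 23% |
| 0.5 | 3.8 | 47% |
| 1.07 | 8.0 | 100% |

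**Step 3: what the other terms would do.** Regress the treatment indicator on the remaining model terms and call the residual r. The months of drift left in the BreeZe coefficient are Σ(r·t)/Σ(r²), with t the calendar month. Time since BreeZe started is coded 0 before the center's start.

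| Terms beside group | Months of drift left |
|---|---|
| Center | 7.5 |
| Center + season (quarters) | 7.6 |
| Center + time since BreeZe started | 2.7 to 3.2 |
| Center + both | 2.2 to 2.4 |
| Center + linear month, or roll-out periods | 0 |

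The ranges run over start- to end-of-month introduction. Season does not remove a linear trend. Time since start removes part of it, but the group coefficient then means the effect at the moment of introduction, which is a different quantity.

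**Step 4: the price of a calendar term.** The variance of the BreeZe coefficient relative to the model with center dummies is 1/Σ(r²) with the term divided by 1/Σ(r²) without it.

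| Added term | Variance ratio | SE ratio |
|---|---|---|
| Linear month | 2.42 to 2.85 | 1.56 to 1.69 |
| Roll-out periods | 3.54 to 3.91 | 1.88 to 1.98 |

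If the model without a calendar term has 80% power, its standardized effect is 1.96 + 0.84 = 2.80. Dividing by 1.56 to 1.69 gives 1.80 to 1.66, which is power of about 44% to 38%. With roll-out periods it is about 32% to 29%. A single 20% allowance for dropout, missing data and time effects together does not cover this.

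**Limit of Step 4.** Uniform accrual implies 31% to 38% controls (14/45 to 17/45). The Results report 42 of 95, or 44%, so accrual was not uniform and the SE ratios are approximate. Repeated measurements would change absolute power but not the direction.

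**The case against.** The strongest reply is that the plan may intend a calendar term and word it badly. Only the continuous option is tied to discharge, the categorical one has no unit, and the sentence begins by citing calendar periods. An allowance for fixed time effects in Sample Size makes sense only if such effects are to be fitted. This much stands: a reader might infer that the plan excludes calendar time altogether, and the text does not show that. What it shows is that no calendar term is committed. Even on the generous reading, calendar adjustment is one of two options to be tested, and the other leaves it out.

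A reader might also infer that every secular change will be counted as BreeZe. That is too strong. Season could absorb a seasonal component, time since BreeZe started reduces a linear trend substantially, and known organizational changes go to sensitivity analyses. But the first two are only candidates, and the third leaves the primary estimate unchanged and does not reach gradual drift.

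A third inference would be that the planned standard errors are wrong. They are not wrong for the model fitted. Omitting the term is a bias problem; the wider interval is the price of removing the bias.

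Finally, a condensed article may leave its full covariate list and the rule for choosing the form of time to an analysis plan, so choosing that form from the data is not pressed here. The mismatch between purpose and time variable, and the claim about sample size, are stated in the article itself.

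**Conclusion.** The point holds in this form: the primary PiH model commits to no calendar-time term, although the protocol names calendar period as the reason for modelling time. The time variable it specifies is follow-up time, and the listed candidates would remove a linear trend partly or not at all. The allowance for fixed time effects in Sample Size has no matching term in the analysis. The claim in Methodological Considerations is wrong, because a larger sample narrows the interval around a biased estimate and does not move it.

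With center dummies only, 7.5 months of any linear drift enters the BreeZe estimate; this rests on the stated dates and even accrual within each phase. The 1.9 to 3.8 points are an illustration at an assumed 0.25 to 0.5 points per month. The documents give no evidence that PiH scores are drifting, or in which direction, so they do not show that the result will be biased, only that the plan as written does not protect against it.

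**What to change.** Before the August 2026 analysis:

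1. Pre-specify a calendar-time term based on discharge date in the primary PiH model, beside group, the two center dummies and follow-up occasion. Linear calendar month with roll-out period dummies as a sensitivity analysis is one workable choice. The linear form assumes a trend common to the three centers; period dummies relax linearity at a higher cost in precision, and would also be defensible as the primary form.
2. State that time since discharge describes follow-up, and give the unit of any categorical time variable.
3. Use the same terms for the secondary patient outcomes.
4. Reword Methodological Considerations so that time confounding is handled in the analysis model, in line with the allowance in Sample Size.
5. State openly that precision and power will be clearly lower than the sample size section implies.

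No new data are needed: Data Management lists discharge date in the eligibility file, and the key file allows it to be linked to the study code. The cost is the loss of precision shown above, an SE about 1.55 to 1.7 times larger with a linear term and nearly twice as large with period dummies. It falls on a study that enrolled 95 of the planned 146.
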